### Design

At present, all Head Start mothers are given social work and case management services and education by the Head Start team regarding the importance of physical and mental health care. Mothers are screened for mental health needs during their "strength and needs assessment" by the case management staff and given referrals to care when necessary. However, there is no systematic depression prevention strategy, and there is no tested, evidence-supported mechanism to get depressed parents quality mental health care.

Study design. Parallel group, RCT involving mothers whose children attend Head Start - a comprehensive preschool program for low-income children birth to 5. Eligible mothers will be randomized to receive PSE or standard of care at Head Start. Both groups will be followed for 12 months.

Participants. 230 Head Start mothers (115, PSE; 115, control) will be enrolled in the at-risk stratum.

Randomization. The unit of randomization will be the mother. Investigators and data collectors will be blinded to study allocation. We could have chosen a number of study designs, including cluster randomization by caseworker or Head Start center. Cluster randomization, however, has its own set of methodologic shortcomings, notably post-randomization selection bias. Because we also expect high intra-class correlation among families within the same Head Start center, a cluster design on this basis would create unrealistic sample size requirements. Conversely, the only substantial drawback of a parallel design would be a conservative bias in favor of the control arm due to intervention spillover. However, because control subjects will not have access to trained educators, we anticipate such effects to be minimal. Randomization will occur independently within each Head Start site, within strata defined by the presence or absence of depression history. We will randomize 1:1 within randomly varying blocks of 2 and 4.

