#### Outcome measures (\*denotes primary outcome measure)

| Outcomes                                                      | Operationalization of variable                                    | Timing of data collection after baseline |
|---------------------------------------------------------------|-------------------------------------------------------------------|------------------------------------------|
| i. Problem Solving Skills*                                    | Calculated problem solving index from SPSI-R                      | 6, 12 months                             |
| ii. Incident rate of moderate to severe symptomatic episodes* | QIDS score $\geq 11$ , corresponding to 'moderate' symptomatology | 2, 4, 6, 8, 10, 12 months                |
| iii. Depressive symptoms over time*                           | Mean QIDS scores over time                                        | 2, 4, 6, 8, 10, 12 months                |
| iv. Social and parenting functioning                          | Mean SAS-SR and PSI scores                                        | 6, 12 months                             |
| v. Receipt of mental health services                          | Standardized questionnaire                                        | monthly recall                           |
| vi. Head Start attendance                                     | Head Start records, analyzed as monthly absence rates             | monthly reports                          |

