### Sample Size Justification

Based on empiric longitudinal data that we have collected among a cohort of Head Start mothers, we describe the size of detectable interventional effects with adequate statistical power for each primary outcome. All estimates assume 80% power and a two-sided alpha of 0.05.

- i. Problem solving skills. The mean problem solving (SPSI-R) score among mothers in our observational study is 12.2, (SD 2.5); women with  $\geq$  moderate depression symptoms have a mean score of 14.7 (SD 2.2) and those with  $\leq$  mild symptoms have a mean score of 9.8 (SD 2.8;  $p > 0.0001$ ). Using a two-sample t-test, a sample size of 100 per group will be able to detect a very granular one-point difference in mean SPSI-R scores between study groups (a standardized effect size of 0.4).

- ii. Incident rate of moderate to severe symptomatic episodes. Using poisson regression analysis, with 100 subjects in each study group and a poisson rate of 1.2 spikes per 5 follow-up assessments in the control group (according to our current data), we can detect a reduction in the rate of spikes to 0.8 in the treatment group – a 33% reduction in symptomatic episodes.
- iii. Depressive symptoms over time. In our longitudinal data, we have observed the following mean QIDS scores for each follow-up month and assume these values for the control group in the planned study: 8.2; 7.6; 7.5; 6.9; 7.2 (common SD, 5.9). We hypothesize that the following mean QIDS scores in the treatment group would be achievable and clinically significant: 7.2; 6.6; 5.5; 4.4; 4.2, resulting in a mean difference of 3 points in QIDS scores across study groups (note: a 3-point difference in QIDS scores, in the majority of cases, would move a subject across a clinical cutoff corresponding to mild, moderate or severe symptoms). Using a two group repeated measures design analyzed by generalized estimating equations or mixed linear models, noting within-subject correlations of 0.7 for values separated in time by one month and 0.6 for those separated for two months or more in our longitudinal analysis), we can detect the above differences in the means between groups over time with 100 subjects per study group.

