Therefore, with an analyzable sample of 100 subjects per study group, we will be able to detect with adequate statistical power differences in problem solving scores, incident rates of elevated QIDS scores, and mean QIDS scores over time that are of clear clinical relevance. Based on our current data, we estimate that 20% of mothers approached will refuse participation; 70% will meet eligibility criteria; and we will experience a 15% attrition rate over the course of the study. Therefore, to ensure that we assess outcomes in 200 study subjects, we will approach 410 subjects and randomize 230. This sample size will be readily available from our ABCD Head Start sites, which average 100 families per site.

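### Both QIDS power calculations assume five follow-up assessments where the trial schedules six, and the event-rate calculation leaves out the within-mother correlation that the same section reports

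*Protocol*

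**What the plan says.** In the Protocol's Sample Size Justification, "All estimates assume 80% power and a two-sided alpha of 0.05". The analysable number is 100 per arm ("with an analyzable sample of 100 subjects per study group"), with 1:1 allocation.

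- **Episode rate.** The calculation takes "a poisson rate of 1.2 spikes per 5 follow-up assessments in the control group" and concludes that "we can detect a reduction in the rate of spikes to 0.8 in the treatment group", a 33% fall. It gives no interval between the five assessments.
- **Mean QIDS.** Five control means are assumed for the planned study, "8.2; 7.6; 7.5; 6.9; 7.2 (common SD, 5.9"), beside five treatment means (7.2, 6.6, 5.5, 4.4, 4.2). The section reports "within-subject correlations of 0.7 for values separated in time by one month" and 0.6 for values two or more months apart, both from the earlier cohort.

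The outcome table lists QIDS for both outcomes at "2, 4, 6, 8, 10, 12 months", which is six assessments. Item 8 of Procedure agrees: QIDS is collected every two months and follow-up starts at month 2. Data Analysis compares both outcomes over the full 12 months, using Poisson regression for the rate and group-by-time effects for the means.

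**The concern.** Two of the three starred primary outcomes are powered on a number of assessments that the trial will not use. No rate is given for six visits and no sixth pair of means is supplied, so a reader cannot tell what power the planned schedule has. The 0.7 correlation fits no pair of scheduled visits, since the closest are two months apart.

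A second matter lies in the same calculation. The section reports that QIDS scores within a mother correlate at 0.6 to 0.7, yet it treats counts of high scores on the same instrument as plain Poisson. If the same mothers tend to be elevated at several visits, the counts vary more than Poisson allows and the stated power is too high. This would be so with five visits or with six.

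**Working it through.** **Inputs from the Protocol.** 100 per arm; two-sided 0.05; rates 1.2 and 0.8 per five assessments, which is 0.24 and 0.16 per assessment; SD 5.9; differences in means 1.0, 1.0, 2.0, 2.5, 3.0 (average 1.9); correlations 0.7 (one month) and 0.6 (two months or more); six two-monthly visits.

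**1. The stated Poisson figure.** Wald test on the log rate ratio: power = Φ( ln(λ₁/λ₂) / √[(1/λ₁ + 1/λ₂)/n] − 1.96 ).
- Standard error: √[(1/1.2 + 1/0.8)/100] = 0.1443.
- ln 1.5 = 0.4055, and 0.4055/0.1443 = 2.81.
- Power = Φ(0.85) = 80.2%. The number needed for 80% is 99.5 per arm.

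The stated figure reproduces.

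**2. Six visits at the same rate per assessment (assumption).** Rates become 6 × 0.24 = 1.44 and 6 × 0.16 = 0.96.
- Standard error: √[(1/1.44 + 1/0.96)/100] = 0.1318, and 0.4055/0.1318 = 3.08.
- Power = 86.8%, and 83 per arm would give 80%.
- With 100 per arm, the detectable rate ratio at 80% power is 0.694 (1.44 to 1.00), a 31% reduction.
- If 1.2 and 0.8 are instead totals over all six visits, power stays at 80.2%.

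**3. Mean QIDS, group-by-time test.** With a common correlation ρ, the noncentrality is (n/2) × Σ(dⱼ − d̄)² / [SD²(1 − ρ)], on one degree of freedom fewer than the number of visits. Here SD²(1 − ρ) = 34.81 × 0.4 = 13.92.

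| Design | Σ(dⱼ − d̄)² | Noncentrality | Power |
|---|---|---|---|
| Five visits, 0.7 adjacent, 0.6 otherwise (general form) | 3.20 | 9.56 | 69% |
| Five visits, 0.6 throughout | 3.20 | 11.49 | 78% |
| Six visits, 0.6, sixth difference 1.9 (assumption) | 3.20 | 11.49 | 75% |
| Six visits, 0.6, sixth difference 3.0 (assumption) | 4.21 | 15.11 | 87% |

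The Protocol does not say which test it powered. On five monthly points the average difference has 77% power and a linear slope 84%, so its 80% for this outcome can be bracketed but not reproduced exactly. For the average difference on six visits, power is 80% or 86% with a sixth difference of 1.9 or 3.0.

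**4. Within-mother correlation in the counts.** Assume that each assessment at or above the cutoff counts once and that elevation is a normal latent score crossing a threshold, with the reported QIDS correlation applying to that score. With k visits, elevation probability p and joint probability p₁₁ for two visits, the count variance at a common correlation is k·p(1 − p) + k(k − 1)(p₁₁ − p²).

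Six visits, 0.6 throughout:
- Control: p₁₁ = 0.1272. Variance = 6 × 0.24 × 0.76 + 30 × (0.1272 − 0.0576) = 3.18. Variance/mean = 3.18/1.44 = 2.2.
- Treatment: p₁₁ = 0.0734. Variance = 6 × 0.16 × 0.84 + 30 × (0.0734 − 0.0256) = 2.24. Variance/mean = 2.24/0.96 = 2.3.
- Standard error: √[(3.18/1.44² + 2.24/0.96²)/100] = 0.199. 0.4055/0.199 = 2.04. Power = Φ(0.08) = 53%.

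The same method on five visits gives 49% with 0.7 for adjacent visits and 0.6 otherwise, and 51% with 0.6 throughout.

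With a fixed variance-to-mean ratio instead (assumption), six-visit power is 80% at a ratio of 1.2, 71% at 1.5 and 59% at 2. Five-visit power at those ratios is 73%, 63% and 51%.

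**The case against.** The section says openly that its inputs come from an earlier cohort, and its Poisson arithmetic is right on those inputs. The 0.7 is reported as a cohort finding and may not have driven the result; the applicable 0.6 stands beside it. A sixth visit at the same rate raises Poisson power, so the stated 33% is slightly conservative. All of this stands. It shows that the visit mismatch is one of documentation and does not expose a shortfall in numbers.

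It does not remove the point. The cohort values are expressly adopted for the planned study, and that study has six visits.

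A reader might infer three stronger things that the Protocol does not support:
- **That both calculations use monthly spacing.** The episode-rate item gives no spacing. For the means, monthly spacing is only suggested by the reference to follow-up months and the one-month correlation. The five means carry no month labels, so it cannot be shown which scheduled visit lacks a value.
- **That five versus six visits leaves the trial underpowered.** For the Poisson outcome the effect goes the other way or is nil.
- **That the fall to about 50% comes from the visit count.** It comes almost wholly from within-mother correlation and appears with either count. The exact figure also depends on a threshold model that the Protocol does not state.

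**Conclusion.** The point holds as an inconsistency that is cheap to repair. The power statements for both QIDS outcomes describe five assessments, and the trial has six.

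- **Episode rate, visit count alone:** plain-Poisson power moves from 80% to about 87% and the detectable reduction from 33% to about 31%, if the rate per assessment is constant. Nothing changes if 1.2 is the 12-month total.
- **Mean QIDS, group-by-time:** about 75% to 87% for a sixth difference between 1.9 and 3.0. Whether the stated 80% is met turns on a value that the Protocol does not give.
- **Episode rate, correlation:** this separate weakness is the larger one. With 0.6 carried into the counts, power on six visits is about 53%. That figure rests on the normal-threshold model and on counting every elevated assessment. Under a fixed ratio, six-visit power falls below 80% once variance/mean exceeds about 1.2.

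The visit mismatch gives no ground for changing the number randomised.

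**What to change.** Rewrite the two QIDS paragraphs of the Sample Size Justification:

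1. Put the episode rate on six two-monthly assessments (1.44 versus 0.96), or state that 1.2 is the total over 12 months.
2. State which months the five listed means refer to, and add a sixth pair.
3. Use correlation 0.6 throughout, and name the test that was powered (group-by-time, average difference or slope).
4. Restate power for the episode rate with a count variance that allows for within-mother correlation, giving the variance-to-mean ratio assumed and a range around it. The cohort behind the 1.2 should supply that ratio directly.

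The cost is a recalculation and two reworded paragraphs. Sample size, visits and conduct stay as they are.

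### Randomising 230 mothers at the protocol's own 15% attrition yields about 195 assessed, not the 200 it says this ensures; the effect on power is about one percentage point

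*Protocol*

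**What the plan says.** The Sample Size Justification ties its power statements for all three primary outcomes to 100 mothers per group, at 80% power and two-sided alpha 0.05. For problem-solving skills, for example, "a sample size of 100 per group will be able to detect" a one-point difference. The summary paragraph repeats the premise: "with an analyzable sample of 100 subjects per study group".

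It then sets the recruitment assumptions: "20% of mothers approached will refuse participation; 70% will meet eligibility criteria". For losses after randomisation its planning assumption is: "we will experience a 15% attrition rate over the course of the study". From these it concludes: "Therefore, to ensure that we assess outcomes in 200 study subjects, we will approach 410 subjects and randomize 230".

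The Design section carries the number forward: "230 Head Start mothers (115, PSE; 115, control) will be enrolled in the at-risk stratum". The Study Summary and the Procedure section also give 230. The only other retention figure is in the Procedure section (item 8), which reports follow-up above 85% in the team's related studies.

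**The concern.** The attrition assumption and the promised number assessed stand in consecutive sentences, and the second does not follow from the first. If 15% of those randomised are lost, 230 is too few to leave 200.

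This matters because 100 per group leaves almost no reserve. On the protocol's inputs it gives just over 80% power for the two primary outcomes that can be checked directly, so any shortfall takes the calculated power below the stated level. The sample-size statement is also likely to be carried into the trial report, where a reader can check it in one line.

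**Working it through.** **Inputs from the protocol.** Target 200 assessed (100 per group); attrition 15%; 230 randomised 1:1; 410 approached; 20% refusal; 70% eligible; two-sided alpha 0.05. SPSI-R: difference 1 point, SD 2.5, standardised effect 0.4. Episodes: 1.2 per mother in the control group against 0.8 under treatment.

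**Reproducing the plan's figures.**
- Approached: 230 / (0.80 x 0.70) = 410.7, against the stated 410. Going forward, 410 x 0.80 x 0.70 = 229.6. This step divides by the expected yield and is consistent with 230.
- Randomised: 200 x 1.15 = 230 exactly. No formula is shown, so this is an inference about where the number came from.

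**Checking the attrition step.**
- Expected number assessed: 230 x (1 - 0.15) = 195.5, or 97.75 per arm. This is 4.5 mothers short.
- Number to randomise for 200: 200 / (1 - 0.15) = 235.3, so 236 (118 per arm). The matching number approached is 236 / 0.56 = 421.4, about 422.
- Break-even attrition with 230 randomised: 1 - 200/230 = 13.0%.
- If losses are independent at 15% (my assumption), the binomial probability that at least 200 of 230 are assessed is about 23%.

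**Power at the two sizes.** The t-test row is the exact two-sample t-test at d = 0.4. The Poisson row is a Wald test on the log rate ratio, with power = Phi(z - 1.96) and z = ln(1.2/0.8) / sqrt(1/(1.2n) + 1/(0.8n)). At n = 100, z = 0.4055 / 0.1443 = 2.809. At n = 97.75, z = 0.4055 / 0.1460 = 2.777.

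| Primary outcome | 100 per arm | 97.75 per arm |
|---|---|---|
| SPSI-R, t-test | 80.4% | 79.5% |
| Episodes, 1.2 vs 0.8 | 80.2% | 79.3% |

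The normal approximation for SPSI-R gives 80.7% and 79.9%.

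**Detectable effects at 80% power.**
- SPSI-R: d = 0.398 (0.995 points) at 100 per arm and d = 0.403 (1.007 points) at 97.75. Both round to the stated 0.4 and one point.
- Episodes: a detectable treatment-group rate of 0.801 at 100 per arm and 0.797 at 97.75. Both round to the stated 0.8.

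**Mean QIDS.** The protocol does not fix the exact test behind this power statement. For one possible form, a linear group-by-time contrast over the five listed means (SD 5.9, correlation 0.7 between adjacent assessments and 0.6 otherwise), power is 85.3% at 100 per arm and 84.5% at 97.75. The level depends on the form of test chosen. In this form the change is again about one point.

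**The case against.** The strongest case on the other side is that nothing of substance changes. Several parts of it stand.

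- **Size.** A loss of under one percentage point is small beside the uncertainty in any planning SD, event rate or attrition figure, and the detectable effects survive at their stated rounding. This stands.
- **Partial follow-up.** The 15% is loss over the whole study. Two of the three primary outcomes use repeated QIDS scores, analysed by Poisson regression and by GEE or mixed models, which can use data from mothers who leave early. SPSI-R is also collected at 6 months, when cumulative loss should be lower. So 97 to 98 per arm may understate the information available. It does not rescue the sentence, which promises a number of mothers assessed.
- **A sixth assessment.** The planning rate is per five assessments, while the outcome table schedules six. If the per-assessment rate carries over (an assumption), the rates become 1.44 and 0.96, and Poisson power at 97.75 per arm is 86.0%. On that reading the schedule more than offsets the shortfall for this outcome. The protocol's own power statement, however, uses 1.2 and 0.8.
- **Retention.** Past follow-up above 85%, paid telephone alternatives for the 6- and 12-month interviews, and cell phones for those who need them make 13% attrition plausible. The protocol nevertheless plans on 15%.

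A reader might go further and infer that the trial is materially underpowered, or that the inflation formula is known to be wrong. The document supports neither. The loss is about one point, and the origin of 230 is inferred from an exact match. Nor does this point show that the other planning inputs are optimistic.

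**Conclusion.** The stated figure is wrong as written. With 15% attrition, 230 randomised gives an expected 195 or so assessed mothers, and nothing elsewhere in the protocol closes the gap to 200. The arithmetic rests only on the protocol's numbers, reading 15% as the share of randomised mothers whose outcomes are not assessed.

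The weight is minor. Calculated power for SPSI-R and for the episode rate drops just below the stated 80%, assuming the protocol's SD, effect and rates and complete loss of the mothers who leave. No detectable effect changes at its stated precision, and no design or analysis decision turns on it. It is an inconsistency to correct in the text, not a reason to enlarge the trial.

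**What to change.** Keep 230 randomised. In the Sample Size Justification, replace the assurance of 200 assessed with an expectation of about 195 analysable mothers (97 to 98 per arm) at 15% attrition. Restate power at that number: 79.5% for the SPSI-R t-test, 79.3% for the Poisson comparison at 1.2 against 0.8, and a recomputed value for mean QIDS under whichever model and contrast the team used. Alternatively, leave the target at 200 and say that it requires attrition of 13% or less.

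The cost is one sentence and a short recalculation, with a slightly less favourable power statement. Enrolment, budget, procedures and analysis do not change.

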### Data Analysis

Our analysis plan conforms to CONSORT guidelines. We will record the number of families approached, screened, ineligible, and refusing participation. We will assess the success of randomization by comparing baseline characteristics between groups. We will record subject attrition and note all adverse events. To estimate intervention effect, we will conduct an intention-to-treat analysis to compare the difference between intervention and control groups for all primary and secondary outcome measures. The following primary outcomes will be analyzed accordingly:

- i. Problem solving skills. We will employ two sample t-tests to compare mean problem solving scores between groups. If significant baseline differences exist across groups, we will employ linear regression analysis to adjust for these differences.
- ii. Incident rate of moderate to severe symptomatic episodes. We will employ Poisson regression techniques to compare rates of elevations in QIDS scores to  $\geq 11$  (moderate symptomatology) over the 12 months of follow-up.
- iii. Depressive symptoms over time. We will use generalized estimating equations or mixed linear models to examine group-by-time effects on mean QIDS scores over the 12 months of follow-up.

Using generalized mixed models for each of these outcomes (to which the above analytic methods can be extended), we will also investigate the impact of Head Start enrollment site as a clustering effect. As an exploratory analysis, we will also examine additional clustering of PSE clients by educator.

This analysis plan, taken from our grant application, will be reproduced in our IRB application.

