  - d. Quick Inventory of Depressive Symptoms. Beck Anxiety Inventory
  - e. Mental Health Service Use questions (adapted from Collaborative Psychiatric Epidemiology Surveys)
  - f. Medical Outcomes Study – Social Support Survey
  - g. Social functioning (Social Adjustment Scale-Self Report)
  - h. Problem Solving Questions (Social Problem Solving Inventory)
  - i. Substance Use (CAGE-AID and AUDIT)
  - j. Coping Questions (Brief COPE)
  - k. Rosenberg Self-Esteem Scale
  - l. Behavioral Activation for Depression Scale
  - m. Pearlin Mastery Scale
  - n. Stressful Life Events Questionnaire
  - o. Modified PTSD Symptom Scale
  - p. Demographics
  - q. Behavioral Activation Score
6. If randomized to the PSE group, we will employ a team of 4 to 6 research staff (at any given time) to serve as interventionists (referred to as educators or providers). The educators will deliver up to 6 PSE sessions with their clients, each session expected to take 30-45 minutes. Sessions will be delivered either weekly or biweekly, according to the wishes of the subject – with a full course of PSE expected to last 8 weeks. Sessions will be delivered at a location of the subject's choosing. In addition to PSE, intervention subjects will be periodically screened with the PHQ-9 as part of 3 out of the 6 PSE sessions. A score of 15 or greater will require the educator to refer the mother to more definitive mental health care. These referrals will be "activated," meaning that the PSE educators will employ motivational interviewing techniques to help the mothers follow through with the referrals. Lastly, educators will phone their clients monthly to conduct brief "booster session" check-in's.
- Request to audiotape a randomly selected PSE will be embedded in the initial consent form; this will be offered to all subjects for the sake of monitoring treatment fidelity. It will be made clear that subjects can refuse audiotaping but still partake in the rest of the study.
7. Control group: We have chosen our control group to best approximate "usual care" in Head Start. Thus, families will be followed by their Head Start caseworkers, and screened periodically for depression when deemed necessary by Head Start staff, per their usual routine. Referrals will be made

according to criteria specified in the grant application.

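### The primary problem-solving (SPSI-R) test discards the baseline score and can be biased by dropout that differs between arms; for QIDS the choice between GEE and a mixed model is left open

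*Protocol*

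**What the plan says.** The Data Analysis section of the protocol commits to intention-to-treat for every primary and secondary outcome: "we will conduct an intention-to-treat analysis to compare the difference between intervention and control groups for all primary and secondary outcome measures". It then names a method for each primary outcome.

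- **Problem solving (SPSI-R, 6 and 12 months):** "We will employ two sample t-tests to compare mean problem solving scores between groups". Adjustment is conditional: "If significant baseline differences exist across groups, we will employ linear regression analysis to adjust for these differences".
- **Depressive symptoms (QIDS, every two months):** "We will use generalized estimating equations or mixed linear models to examine group-by-time effects on mean QIDS scores over the 12 months of follow-up".
- **Extension:** "Using generalized mixed models for each of these outcomes (to which the above analytic methods can be extended"). The stated purpose of this extension is to study clustering by Head Start site.

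The Sample Size Justification expects 15% attrition and randomizes 230 mothers "to ensure that we assess outcomes in 200 study subjects". Item 5 of the Procedure section places both SPSI-R and QIDS in the baseline survey, completed before randomization.

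**The concern.** A two-sample t-test at a visit can use only mothers who have a score at that visit. A mother who is lost contributes nothing, although her baseline SPSI-R is on file. A mother seen at month 6 but not at month 12 contributes nothing to the 12-month comparison. If the mothers lost from one arm differ systematically from those lost from the other, the remaining groups are no longer comparable, and the unadjusted test cannot correct for it.

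The conditional regression is a weak safeguard. A significance check on baseline differences addresses chance imbalance at randomization, whereas the problem here is imbalance created later by dropout.

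Dropout that differs by arm is plausible, though not established. PSE mothers have up to six sessions, after which "educators will phone their clients monthly to conduct brief" booster check-ins, so the amount of study contact differs by arm. The protocol also reports that SPSI-R tracks mood (mean 14.7 with moderate or worse symptoms, 9.8 with mild or fewer), so dropout related to mood would also be related to SPSI-R.

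For QIDS the two permitted methods are not interchangeable. Unweighted GEE is in general not protected when dropout depends on earlier QIDS scores. A likelihood-based mixed model is, provided those scores are in the model and the model is correctly specified.

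**Working it through.** **1. The plan's own figure.** Inputs from the Sample Size Justification: difference 1 point, SD 2.5, two-sided alpha 0.05, power 80%. Per arm, n = 2(1.960 + 0.842)² × 2.5² / 1² = 98.1, so 99. With 100 per arm, power is 80.7% (80.4% by the noncentral t). The stated 100 per group is reproduced.

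**2. Who enters the t-test.** The planned 200 of 230 is 87%. At 15% attrition, 230 × 0.85 = 195.5, about 98 per arm, with t-test power 79.6%.

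**3. Bias formula.** Let d be the proportion lost in an arm and gap the mean score of those lost minus the mean of those retained. The retained mean is too low by d × gap. With the same gap in both arms and no true effect, the PSE-minus-control bias is (d_control − d_PSE) × gap. The protocol gives no dropout by arm, so 10% PSE and 20% control are assumed.

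- Standard error: 2.5 × √(1/103.5 + 1/92) = 0.358.
- Gap 1.0: bias 0.10 × 1.0 = 0.10, type I error 5.9%.
- Gap 2.5: bias 0.25, type I error 10.7%.
- Gap 4.9 (14.7 − 9.8): bias 0.49, type I error 27.7%. This is an extreme bound: every mother lost would have moderate or worse symptoms and every mother retained mild or fewer.
- With 15% lost in each arm and equal gaps, the bias is 0.

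**4. Simulation with dropout driven by baseline SPSI-R.** 115 per arm, no true effect, SD 2.5. The baseline-to-follow-up correlation r = 0.5 to 0.7 and all dropout mechanisms are assumptions.

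| Dropout | t-test bias (points) | t-test type I error |
|---|---|---|
| 10% of PSE at random; 20% of controls, log-odds 1.0 per baseline SD | about 0.2 to 0.3 | about 10 to 14% |
| Same mechanism in both arms, 10% vs 20% | about 0.1 to 0.15 | 6 to 7% |
| 15% in each arm, opposite mechanisms (r = 0.6) | 0.39 | 20% |
| 15% in each arm, same mechanism | 0 | 5% |

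In the first and third rows, including baseline SPSI-R brings the bias to about 0 and type I error to about 5%. Higher SPSI-R goes with worse symptoms in the protocol's data, so losing high-scoring controls makes the remaining controls look better and the bias runs against PSE. Exchanging the arms' mechanisms reverses the sign.

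**5. The conditional adjustment.** In the first scenario, applying the significance check to all 230 mothers leaves bias of 0.21/0.25/0.29 points and type I error of 9%/10%/13% at r = 0.5/0.6/0.7. Applied only to mothers with follow-up, about half the bias remains (0.12 to 0.16), with type I error about 6%.

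**6. Precision when dropout is harmless.** At 98 per arm the unadjusted standard error is 2.5 × √(2/98) = 0.36. Adjustment multiplies it by √(1 − r²), giving 0.31 at r = 0.5 and 0.26 at r = 0.7.

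**7. QIDS.** The protocol's control means, SD 5.9 and correlations 0.7/0.6 were used, with no true effect. Bias is at the last visit.

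| Dropout depends on last observed QIDS | GEE, independence | Mixed model |
|---|---|---|
| 10% PSE vs 20% control | 0.38 | 0.03 |
| About 15% each, opposite mechanisms | 1.07 | 0.02 |
| Equal rate and mechanism | about 0 | about 0 |

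With an exchangeable working correlation, a separate simulation (about 11% vs 22 to 24% lost) gave GEE bias of 0.04 to 0.24 points. The hypothesized differences are 1.0, 1.0, 2.0, 2.5 and 3.0, so 9.5/5 = 1.9 on average. When dropout depends on the unseen QIDS score and differs between arms, both methods are biased: 0.47 to 1.25 points for independence GEE and 0.19 to 0.45 for the mixed model.

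**The case against.** Three stronger readings are tempting, and the protocol does not support them.

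- **That the intention-to-treat promise is untrue.** Its core meaning is analysis in the arm assigned. Nothing in the Data Analysis section excludes a mother for missing sessions, and a t-test on available scores does not contradict that. The narrower fact is that not every randomized mother contributes to the SPSI-R result.
- **That two primary results will be biased.** No dropout by arm is given, and equal loss by the same mechanism produces none. For QIDS, the same sentence that permits GEE also permits mixed linear models, which were essentially unbiased when dropout depended on observed scores.
- **That control mothers have only research calls.** Their caseworkers follow them, and all Head Start mothers receive case management. Incentives, reminders, telephone interviews in place of visits, and cell phones are described without distinction by arm, and related studies kept follow-up above 85%. What remains is extra educator contact in the PSE arm.

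The size of the effect is also fairly contested. The 10 to 14% figure needs unequal rates and unequal mechanisms together; with the same mechanism it is 6 to 7%. The larger GEE biases assume an independence working correlation, which the protocol does not name. Missing-data handling and sensitivity analyses commonly belong in a statistical analysis plan, which is not shown, so their absence is no fault.

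What stands is what the protocol itself fixes: an unadjusted t-test as the SPSI-R method, adjustment dependent on a significance check, and an unresolved choice for QIDS. The mixed-model extension does not settle this, because it is offered to investigate site clustering.

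**Conclusion.** The point holds in a limited form and is a worthwhile, inexpensive improvement. For SPSI-R, the named analysis leaves out information already collected. Depending on how dropout falls, the cost ranges from lost precision alone (standard error 0.36 instead of 0.26 to 0.31) to bias of about 0.1 to 0.3 points on a 1-point target, with type I error of about 6 to 14% when controls are lost at twice the PSE rate. Opposite mechanisms at equal rates can give more (0.39 points, 20%), so equal dropout rates alone do not rule bias out. The direction depends on which mothers leave which arm; in the scenarios worked here it is against PSE. For QIDS, the weakness is only that the choice of method is open. These sizes rest on assumed dropout rates, mechanisms and correlations, since the protocol gives only an overall 15%.

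**What to change.** **SPSI-R:** make the primary analysis a mixed linear model of the 6- and 12-month scores, with baseline SPSI-R always included, either as a covariate or as an outcome occasion. Delete the condition that baseline differences must first be significant. Keep the t-test as a sensitivity analysis.

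**QIDS:** name the likelihood-based mixed linear model, with baseline QIDS included, as the primary method in place of the open choice.

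The protocol already names mixed models for each primary outcome, so this promotes a method it contains and needs no new data. The cost is a change of wording, a correlation structure to specify in advance, a little more programming, and a result less simple to present than a t-test. The model does not remove bias if dropout depends on unobserved scores.
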